### Blinding

Participants will be blinded to the treatment by using encapsulating medications through a third party. The nurse and technician performing clinic blood pressure, and transthoracic echocardiograms will also be blinded to reduce any potential bias in the reporting of outcomes. Clinicians prescribing the antihypertensives will not be blinded to treatment allocation as the titration protocol is treatment-specific. Although a possible limitation, we anticipate that any treatment bias will be minimal given that the prescribed treatment will be driven by the study protocol and up-titration of treatments will be based on clinic blood pressure measurements performed by the nurse (blinded to treatment allocation), and direct renin concentration values measured at the hospital laboratory (for the MRA arm only).

### Study objectives

The primary objective will be to assess the change in mean clinic systolic blood pressure from baseline to week 48 and to determine the total defined daily dose of antihypertensives required to achieve the target blood pressure. The ‘defined daily dose’ is described by the World Health Organization as the average maintenance dose per day for a drug used for its main indication in adults and is a measure of drug utilization [22]. The defined daily dose of spironolactone is 75 mg/day, perindopril 5 mg/day, and amlodipine 5 mg/day [22].

The secondary and exploratory objectives of this study are summarized in Table 2.

**Table 2 Tab2:** Study objectives.

Primary	To evaluate the -change in mean seated clinic systolic blood pressure from baseline to week 48 compared with standard antihypertensive treatment. -total defined daily dose of antihypertensives required to achieve target blood pressure with MRA compared to standard antihypertensive treatment.
Secondary	To evaluate the effect of MRA compared with standard antihypertensive treatment on the: -change in mean seated clinic diastolic blood pressure from baseline to week 48 compared with standard antihypertensive treatment. -change in mean seated clinic systolic and diastolic blood pressure from baseline to week 24. -change in systolic and diastolic blood pressure on ambulatory blood pressure monitoring from baseline to week 48. -time to achieve the target blood pressure. -the proportion of participants that achieved target blood pressure at week 48. -change in the left ventricular mass index and global longitudinal strain on transthoracic echocardiogram from baseline to week 48. -change in endothelial function measured by EndoPAT (Itamar Medical, Israel) from baseline to week 48. -change in 24-h urinary microalbumin excretion from baseline to week 48. -the proportion of participants that discontinued trial medication due to adverse effects. -the proportion of participants who developed hyperkalemia. -change in the quality of life assessed using the SF-36 Quality of Life Questionnaire from baseline to week 48.
Exploratory	To evaluate characteristics that predict response to MRA including age, ethnicity, sex, baseline PAC, DRC, ARR, urinary aldosterone, urinary sodium, post-saline suppression test PAC (measured by LCMS and radioimmunoassay), monocyte-based transcriptomic markers and plasma and urinary steroid profiles.

*ARR* aldosterone to renin ratio, *LCMS* liquid chromatography-tandem mass spectrometry, *MRA* mineralocorticoid receptor antagonist, *PAC* plasma aldosterone concentration, *DRC* direct renin concentration.

### Data collection and management

The medical history, examination findings, medication side effects, compliance, and investigation results will be collected at each study visit (Table 3) and entered via the secure web-based data management system, REDCap. Data entry will be performed by the investigators. Data logic and consistency checks are programmed into the data entry forms so that data entry errors can be caught in real time, and queries are auto-generated. Data generated will be held in strict confidence. No information concerning the trial or the data will be released to any unauthorized third party without the prior written approval of the Hudson Institute of Medical Research.

**Table 3 Tab3:** Data collection schedule.

		Week						
	–6	–2	0	6	12	24	36	48
**Enrolment**								
*Informed consent*	x							
*DRCx2, PACx2, ARR x2, UEC, BhCG (if relevant), HBA1C, PTH, calcium, vitamin D, TSH, plasma metanephrines, 24-h urinary cortisol, and saline suppression test*.		x						
*Randomization*			x					
**Intervention**								
*Active: MRA*								
*Control: standard antihypertensives*								
**Assessment**								
*BMI, age, sex, ethnicity, smoking status, ethanol intake, OSA screening*			x					x (weight only)
*Mean clinic blood pressure*	x		x	x	x	x	x	x
*PAC, DRC, ARR, UEC*				x	x	x	x	x
*Fasting glucose, fasting lipid profile, liver function tests*		x						x
*PTH, calcium, vitamin D*								x
*24-h urine sodium, potassium, calcium, aldosterone, and albumin*		x						x
*24-h urine steroid profile*		x						
*FBE, CRP, BNP*		x						x
*Plasma steroid profile*		x						
*Plasma and urine biobank sample*		x						x
*Monocyte gene expression profile*		x						
*ABPM*			x					x
*TTE*			x					x
*Endothelial function*			x					x
*QOL (SF-36 questionnaire)*			x					x
*Compliance assessment*				x	x	x	x	x
*Adverse effect monitoring*				x	x	x	x	x

*ABPM* ambulatory blood pressure monitoring, *ARR* aldosterone to renin ratio, *BhCG* beta-human chorionic gonadotrophin, *BMI* body mass index, *BNP* brain natriuretic peptide, *CRP* C-reactive protein, *FBE* full blood examination, *GLS* global longitudinal strain, *HBA1c* glycosylated hemoglobin, *LFT* liver function tests, *LVMI* left ventricular mass index, *MRA* mineralocorticoid receptor antagonists, *OSA* obstructive sleep apnea, *PAC* plasma aldosterone concentration, *DRC* direct renin concentration, *PTH* parathyroid stimulating hormone, *SST* saline suppression test, *TSH* thyroid-stimulating hormone, *TTE* trans-thoracic echocardiogram.

### Biological specimen collection and storage

Blood and urine biospecimens collected at baseline and the end of the trial will be frozen and stored at Monash Pathology and may be retrieved to measure new markers of low-renin hypertension and any subtypes identified in this trial. All other biospecimens will be discarded.

### Sample size calculation and statistical analysis

The sample size estimation will be based on the two primary objectives. In a study of hypertensive patients, Weinberger et al showed that after 16 weeks of treatment, systolic blood pressure among patients with low-renin hypertension (renin <9.4 mU/L) was reduced by 17.2 mmHg in the eplerenone group compared with 5.4 mmHg in the losartan group (no standard deviations were reported) [16]. Assuming a similar drop in systolic blood pressure between treatment groups with an equal standard deviation of 10 mmHg for the change in blood pressure, a minimum sample size of 24 patients per arm would be required. For the second primary endpoint of the defined daily dose required to achieve target blood pressure, a comprehensive systematic review of the literature was conducted, but no previous trials reported the expected defined daily dose for either spironolactone or perindopril in low-renin hypertension. Therefore, in the absence of such information, a large effect size will be assumed (Cohen’s d = 0.8). For this effect size, a minimum sample size of 50 patients per group is needed. The two sample size estimations account for 90% power in the study, with a Bonferroni family-wise error rate of 0.025 (two-sided) and a 20% attrition. Bonferroni multiplicity was considered because the outcomes from this study would be confirmative, and the defined daily dose and blood pressure change are presumed to be closely related outcome measures for blood pressure control. Hence the target sample size for this study is 100 patients (50 randomized to each arm of the study).

Participants will be recruited from the Endocrine Hypertension Clinic at Monash Health. In addition to referrals from other specialists, the Endocrine Hypertension research group has established a relationship with over 40 general practice clinics and 200 practitioners who routinely refer patients to the clinic.

Analysis of the efficacy of each intervention will be performed on an intention-to-treat basis. All randomized patients with a baseline assessment and at least one post-baseline assessment will be included in the statistical analysis. Safety analyses will include all randomized patients who received at least one dose of study medication. An additional per-protocol analysis will be considered in the case of non-compliance and/or medication non-adherence. All data will be analyzed as observed and no data imputation is anticipated unless significant missing data is observed.

A generalized linear model will be used to conduct a between-group comparison for the systolic blood pressure, defined daily dose of antihypertensives, left ventricular mass index, global longitudinal strain, endothelial dysfunction, and 24-h urinary microalbumin excretion. If some participants do not achieve target blood pressure, the data will be treated and analyzed using methods for right censored data and between groups comparison will be done using Kaplan–Meier curves and the log-rank test. The difference in the change in blood pressure between groups will be estimated based on the interaction between the time and group variables using a mixed-effects model. A Cox proportional hazards model will be used to assess and compare the time to achieve target blood pressure in the MRA and standard treatment groups. The chi-squared test will be used for between-group comparison of the proportion of participants who discontinued treatment due to adverse effects or developed hyperkalemia during the treatment period. Data will be analyzed using Stata Statistical Package version 17 or later, R Statistical Package version 3 or later, or SPSS Statistical Package version 28 or later. Adverse effects and serious adverse effects will be tabulated and listed, by the treatment group.

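### The 0.025 that the protocol calls a family-wise error rate is the per-test level; the family-wise rate behind its sample sizes is 0.05

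*Protocol article*

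**What the plan says.** Under *Sample size calculation and statistical analysis*, the protocol article says: "The sample size estimation will be based on the two primary objectives". For systolic blood pressure it takes an earlier trial in which pressure "was reduced by 17.2 mmHg in the eplerenone group compared with 5.4 mmHg in the losartan group". It combines that "with an equal standard deviation of 10 mmHg for the change in blood pressure" and concludes that "a minimum sample size of 24 patients per arm would be required". For total defined daily dose it assumes a standardized difference of 0.8 and arrives at 50 per group, which sets the total of 100.

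On error rates it says "The two sample size estimations account for 90% power in the study", "with a Bonferroni family-wise error rate of 0.025 (two-sided) and a 20% attrition". The reason given is that "Bonferroni multiplicity was considered because the outcomes from this study would be confirmative", together with a presumption that the two endpoints are closely related. The article gives no overall level of 0.05, and the analysis paragraphs that follow state no significance threshold.

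**The concern.** Bonferroni starts from a family-wise error rate and divides it by the number of tests. With two primary endpoints, a family-wise 0.025 means 0.0125 for each, while a per-test 0.025 means a family-wise 0.05. The sentence uses the name of one quantity with what may be the value of the other.

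This matters because the article calls the results confirmatory and this sentence is the only place where it gives an error rate. Someone who applies it as written would test at 0.0125. Someone who infers the intention would test at 0.025. A primary p-value between those two limits would be a success for one and a failure for the other. The stated power holds under only one of the readings.

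**Working it through.** **Inputs, all from the sample-size section**

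- Systolic blood pressure: difference 17.2 − 5.4 = 11.8 mmHg, SD 10 mmHg, so d = 11.8/10 = 1.18.
- Defined daily dose: d = 0.8.
- Power 90%, two-sided tests, 1:1 allocation, 20% attrition.
- Stated sizes: 24 and 50 per arm.

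**Step 1. Reproduce the stated sizes.** The evaluable number per arm is solved from the two-sample t-test and rounded up. Attrition is then applied in the two usual ways: multiplying by 1.2, or dividing by 0.8. Pairs are blood pressure / defined daily dose.

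| Two-sided alpha per test | Evaluable | × 1.2 | ÷ 0.8 |
|---|---|---|---|
| 0.025 | 20 / 41 | **24 / 50** | 25 / 52 |
| 0.0125 (family-wise 0.025 taken literally) | 23 / 47 | 28 / 57 | 29 / 59 |
| 0.05 (no adjustment) | 17 / 34 | 21 / 41 | 22 / 43 |

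Only 0.025 per test returns both stated figures: 20 × 1.2 = 24, and 41 × 1.2 = 49.2, rounded up to 50.

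**Step 2. Check that this does not depend on the formula.** The normal approximation is n = 2(z₁₋α/₂ + z₁₋β)²/d², with z₁₋β = 1.2816.

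- α = 0.025: 2 × (2.2414 + 1.2816)² = 24.82. Then 24.82/1.18² = 17.8, so 18, and 24.82/0.8² = 38.8, so 39. Divided by 0.8, these give 23 and 49, each one patient from the stated figure.
- α = 0.0125: 2 × (2.4977 + 1.2816)² = 28.57. Then 28.57/1.18² = 20.5, so 21, and 28.57/0.8² = 44.6, so 45. With attrition these become 26 or 27, and 54 or 57.

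No combination of formula and attrition rule at 0.0125 gives 24 or 50.

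**Step 3. Family-wise rate implied.** The Bonferroni bound is 2 × 0.025 = 0.05. If the endpoints were independent it would be 1 − 0.975² = 0.0494. Simulation under the global null gives 0.049 at correlation 0, 0.040 at 0.8 and 0.033 at 0.95. The article gives no correlation, so these values are assumptions.

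**Step 4. Power if the label were followed.** Fifty per arm less 20% leaves 40 evaluable. For d = 0.8 the t-test power is 0.899 at 0.025 and 0.843 at 0.0125. The normal approximation agrees: 0.8 × √20 = 3.578; 3.578 − 2.241 = 1.336 gives 0.91, and 3.578 − 2.498 = 1.080 gives 0.86. Blood pressure is hardly affected (0.998 and 0.996).

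**Step 5. What Holm's procedure would add.** Holm tests the smaller p-value at 0.025 and, if that is significant, the other at 0.05. Bivariate normal test statistics were simulated with 40 evaluable per arm, d = 1.18 and 0.8, correlations from 0 to 0.95 and 200,000 runs per setting.

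| Power | Bonferroni | Holm |
|---|---|---|
| Defined daily dose | 0.91 | 0.947 |
| Both endpoints | 0.91 | 0.946 to 0.947 |
| At least one endpoint | 0.999 or more | unchanged |

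The gain is the same at every correlation tried. Blood pressure is almost always significant at 0.025, so the defined daily dose is in effect tested at 0.05. By the t-test the change is from 0.899 to 0.942.

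**The case against.** The strongest reply is that this is a single wrong word. Any statistician who redoes the calculation will find the 0.025 per test, and the sample size, the planned power and the analysis models all stay as they are. That is correct, and it limits the weight of the point. It does not remove it, because the article offers no other error rate against which to correct the sentence. An analysis plan that is not shown could only repeat this sentence or contradict it.

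Some stronger readings do not hold:

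- *That the trial is too small.* At 0.025 per test, 40 evaluable per arm give the stated 90%. The shortfall to 0.84 arises only if the label is taken literally.
- *That plain Bonferroni is a mistake.* It controls the family-wise error under any dependence, and the 90% target is met without Holm. Holm is an efficiency gain, and the final testing procedure may be set out in a document not shown.
- *That close relation between the endpoints is why power is lost to Holm.* Holm does not use the correlation. Close relation only makes Bonferroni conservative, as Step 3 shows.
- *That Holm brings large gains.* With d = 0.5 for blood pressure and a correlation of 0.5, power for blood pressure would rise from 0.50 to 0.60 and power for both endpoints from 0.48 to 0.60. Neither input is in the article, which plans on d = 1.18 and gives no correlation.
- *That Holm is free.* It needs no patients and gives up no error control, but simultaneous confidence intervals become less simple. Recruitment began in August 2022 and prescribers are unblinded, so a change of rule now may need an amendment and must be seen to precede any unblinded data.

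**Conclusion.** The label is wrong. The article's own sample sizes show that 0.025 is the level of each test and that the family-wise rate is 0.05, so the printed rate is off by a factor of two. The consequence is an ambiguous success threshold for two confirmatory endpoints. If the text were followed literally, power for the defined daily dose would be about 0.84 instead of 0.90 with 40 evaluable per arm, and 47 evaluable (57 to 59 randomized, depending on how attrition is applied) would be needed to restore it.

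This rests on the article's stated effects, SD, power and attrition, and on a two-sample comparison of means. The exact match also needs the multiplication by 1.2, but the conclusion does not: every combination tried rules out 0.0125. It is a correction of wording with no effect on the number of patients. The Holm suggestion is optional.

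**What to change.** Replace the phrase with: *two-sided family-wise type I error of 0.05 over the two primary endpoints, controlled by Bonferroni at 0.025 per test*. Keep the total of 100. This costs one sentence and changes no patient number, power figure or analysis.

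Optionally, name Holm's procedure in place of plain Bonferroni: the smaller p-value is tested at 0.025 and, if significant, the other at 0.05. The per-test 0.025 stays as the planning level. The choice should be recorded and dated before anyone sees outcome data by treatment group. The return is about 4 percentage points of power for the defined daily dose and for winning on both endpoints. The price is less simple simultaneous intervals and possibly an ethics amendment. If the sponsor prefers to keep Bonferroni, the label still needs correcting.

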### Trial procedure

Study participants meeting the inclusion and exclusion criteria will be randomized 1:1 via REDCap to either MRA, spironolactone (intervention), or standard care, perindopril+/-amlodipine (control), using a block randomization method. The schedule has been prepared by a biostatistician and uploaded to REDCap and is not available to the clinic staff. Participants on antihypertensive treatment at baseline will undergo a washout period of 2–4 weeks before screening and randomization. If there are clinical concerns, prazosin, a short-acting antihypertensive can be continued until 48 h pre-randomization. The standard care group will receive treatment as per local prescribing patterns and hypertension guidelines [14]. Antihypertensive medications will be titrated as required at 12-weekly intervals until target blood pressure of <140/90 mmHg is achieved in both groups and renin is unsuppressed i.e., >15 mU/L in the MRA group (Fig. 1). The biochemical titration target for the MRA group is based on evidence that treatment adequacy is associated with normalized renin [17]. Participants will be reviewed every 6–12 weeks and treated for a total of 48 weeks. Administration of medication will be standardized to night-time dosing once daily for consistency. Blood pressure measurements will be taken seated in triplicates using an automated blood pressure machine (Omron) and the average of 2nd and 3rd readings will be calculated. Automated office blood pressure measurement has been shown to correlate with out-of-clinic measures [18].

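### Time to target blood pressure is seen at only five visits but is given an ordinary Cox model; with nominal visit times and Breslow ties, the hazard ratio would shrink towards 1 (minor)

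*Protocol article*

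**What the plan says.** The protocol article lists "time to achieve the target blood pressure" among the secondary objectives (Table 2). In the section on sample size and statistical analysis it assigns the model: "A Cox proportional hazards model will be used to assess and compare the time to achieve target blood pressure".

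The observation times are set elsewhere. In Table 3 the row "Mean clinic blood pressure" is marked, after baseline, at weeks 6, 12, 24, 36 and 48. The trial procedure section agrees: "Participants will be reviewed every 6–12 weeks and treated for a total of 48 weeks", and "Antihypertensive medications will be titrated as required at 12-weekly intervals until target blood pressure of <140/90 mmHg is achieved in both groups".

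On size: "Hence the target sample size for this study is 100 patients (50 randomized to each arm of the study"). On software the analysis may use "Stata Statistical Package version 17 or later, R Statistical Package version 3 or later, or SPSS Statistical Package version 28 or later". The article names no tie method and no grouped-time or interval-censored form of the model.

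**The concern.** Attainment of target is not observed when it happens. It is recorded at the first scheduled visit at which the reading is below target. The follow-up therefore offers five possible event times, 6 or 12 weeks apart, and both arms share them. A Cox partial likelihood is built for continuous time with few ties. With tens of events on one time, the result depends on how ties are handled, and the Breslow approximation is biased towards no effect.

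At stake is an understated benefit, and lost power, on the endpoint that describes how fast each strategy controls blood pressure. Neither primary endpoint nor the sample size is affected.

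**Working it through.** **Inputs from the protocol.** 50 patients per arm; visits at weeks 6, 12, 24, 36 and 48. The protocol gives no figure for this endpoint to reproduce: no expected hazard ratio and no expected share at target.

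**Assumptions.** True hazard ratio (HR) 2.0 in favour of faster attainment; 70% of controls at target by week 48; constant hazard; no dropout in steps 1 to 3. These are varied in steps 4 and 5.

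**Step 1: how heavy are the ties?** Control hazard λ = −ln(1 − 0.70)/48 = 0.02508 per week. The share not yet at target is S0(t) = exp(−λt) in controls and S1(t) = S0(t)² in the other arm.

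| Week | S0 | S1 | Control events | MRA events | Total on this time |
|---|---|---|---|---|---|
| 6 | 0.860 | 0.740 | 7.0 | 13.0 | 20.0 |
| 12 | 0.740 | 0.548 | 6.0 | 9.6 | 15.6 |
| 24 | 0.548 | 0.300 | 9.6 | 12.4 | 22.0 |
| 36 | 0.405 | 0.164 | 7.1 | 6.8 | 13.9 |
| 48 | 0.300 | 0.090 | 5.3 | 3.7 | 9.0 |

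Some 80 events fall on five times.

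**Step 2: what Breslow estimates.** With Breslow ties, each visit contributes information on the ratio of per-visit probabilities, not on the ratio of hazards.
- 6-week interval: 0.2599/0.1397 = 1.86.
- 12-week interval: 0.4523/0.2599 = 1.74.

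The Breslow estimate θ solves Σ[d1 − d·r1θ/(r1θ + r0)] = 0, where r1 and r0 are the numbers at risk, d1 the MRA events and d all events at a visit. At θ = 1.79 the five terms are 0.176, 0.143, −0.153, −0.098 and −0.062, which sum to 0.006, essentially zero. A true 2.0 therefore reads 1.79.

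**Step 3: what a grouped-time model estimates.** The complementary log-log model compares ln(1 − p1) with ln(1 − p0).
- 6-week interval: ln(0.7401)/ln(0.8603) = 2.00.
- 12-week interval: ln(0.5477)/ln(0.7401) = 2.00.

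It recovers the true value at every visit.

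**Step 4: other response rates** (large-sample values, true HR 2.0).

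| Controls at target by week 48 | Breslow | Efron | Complementary log-log |
|---|---|---|---|
| 50% | 1.87 | 1.99 | 2.00 |
| 70% | 1.79 | 1.98 | 2.00 |
| 85% | 1.71 | 1.97 | 2.00 |
| 95% | 1.62 | 1.93 | 2.00 |

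At a true HR of 1.0 every method gives 1.00.

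**Step 5: power** (2,000 simulated trials per row, 50 per arm, about 4.5% dropout between visits, Wald test at 5%, true HR 2.0). The control chance per visit is an assumption. Without dropout, a chance p gives 1 − (1 − p)⁵ at target by week 48: 41%, 67%, 83% and 92%.

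| Control chance per visit | Breslow HR / power | Efron HR / power | Power lost (points) |
|---|---|---|---|
| 10% | 1.93 / 61% | 2.02 / 67% | 6 |
| 20% | 1.82 / 74% | 2.01 / 84% | 10 |
| 30% | 1.71 / 73% | 1.99 / 88% | 15 |
| 40% | 1.62 / 64% | 1.96 / 89% | 25 |

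A separate run at 10% gave 60% against 65%, a loss of 5 points. Under no effect, Breslow rejected in 1.1 to 2.5% of trials at control rates of 20 to 40%, and Efron in 4 to 5%.

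**Step 6: does it depend on coding time by nominal visit?** Yes. When visit dates were varied by 7 days, Breslow returned to 1.92 to 1.96, with power matching Efron.

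**The case against.** The strongest reply is that the protocol states no error. It says Cox and never says Breslow, and Cox with Efron ties is close to unbiased here. Tie handling is ordinary SAP detail, and an SAP may exist that settles it. This stands to the extent that a missing tie rule alone would be no finding. What remains is that the protocol pairs a continuous-time model with an outcome it measures at five times, when a model that fits that schedule is available.

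Second, ties arise only if time is coded by scheduled visit, and the protocol does not say that it is. This also stands: actual visit dates remove most of the effect.

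Third, the bias is conservative, and the endpoint is one of eleven secondary objectives. The section also plans Kaplan–Meier curves and a log-rank test if some participants miss target. That sentence does not name its outcome clearly. If it covers time to target, the log-rank test is little troubled by ties: in simulation its power was 84% against 84% for Efron at 20% per visit, and 90% against 88% at 40%. The significance test would then be protected, but not the Cox hazard ratio.

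A reader might also infer from the three permitted packages that the result will depend on which one is used, or that the package could be picked once the data are seen. The document supports neither. It says nothing of how any package treats ties or when the choice is made, and an analyst can set the tie method explicitly.

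**Conclusion.** The point holds in a conditional form and is minor. If time is coded by nominal visit and Breslow ties are used, a true hazard ratio of 2.0 reads about 1.6 to 1.9, and about 5 to 25 points of power are lost against Efron, more as response rises. At 70% of controls at target, the shift is ln(2.0/1.79) = 0.11 on the log scale, roughly half the sampling standard deviation of about 0.21 to 0.24.

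The size rests on assumed hazard ratios and response rates, because the protocol gives none. It would be wrong to conclude that the Cox model is unsuitable as such, or that a false positive becomes more likely: the null estimate stays at 1.00 and type I error is not inflated.

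**What to change.** State that time to target will be analysed with a discrete-time proportional hazards model: complementary log-log link, treatment arm, and a term for each scheduled visit. It still yields a hazard ratio, fits the five-visit schedule and makes tie handling irrelevant. Alternatively, keep the Cox model and specify Efron ties. Either choice should be fixed before database lock, together with whether time is coded by scheduled visit or by actual date.

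The cost is one sentence in the analysis section or the SAP. No new data, visits or patients are needed.
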